### SUMMARY

**Rationale:** Clinical guidelines recommend routine follow up (RFU) with X-ray and clinical visit at 1 year after Total Hip Arthroplasty (THA) and Total Knee Arthroplasty (TKA). However, evidence for (cost-)effectiveness of RFU is lacking. Registry data show excellent survival of THA and TKA and the added value of RFU can be questioned, as revisions are rare and seldom without symptoms. However, replacing RFU with a final follow up within 3 months and thereafter only check-ups on demand (COD), could lead to risks such as missed complications, lower patient satisfaction, or decreased physical function.

**Objective:** To investigate the (cost-)effectiveness of COD compared to RFU at 1 year, up to 2 years after THA and TKA.

**Study design:** A hybrid effectiveness (de-)implementation trial type II, with a stepped-wedge cluster trial design.

**Study population:** Patients scheduled for THA or TKA who experience pain and disability in the knee or hip joint due to osteoarthritis, and aged  $\geq 50$  years at the time of the surgery.

**Intervention:** Check-up on demand (COD) by the patient or healthcare provider (HCP), after a final clinical visit with X-ray within 3 months to diagnose complications and provide instructions when to contact an HCP.

**Comparator:** Routine follow up (RFU) consisting of an X-ray and clinical visit within 3 months and at 1 year after surgery. Patients are welcome to contact an HCP in case of pain, concerns or other symptoms associated with their prosthesis at any time.

**Main study parameters/endpoints:** The main study parameters are clinical and process outcomes. The clinical outcome is patient-reported physical function, measured with the PROMIS questionnaire, 2 years after surgery (1 year after RFU or COD). The process outcome is healthcare consumption, including X-rays and clinical visits.

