## 2. OBJECTIVES

**Primary Objective:** At 2 years after surgery, what is the effect of a final follow up within 3 months combined with check-ups on demand (COD) compared to routine follow-up (RFU) within 3 months and at 1 year after total hip and knee arthroplasty (THA and TKA) on physical function (effectiveness) and clinical visits (implementation)?

**Secondary Objective(s):** At 2 years after surgery, what is the effect of a final follow up within 3 months combined with COD compared to RFU within 3 months and at 1 year after THA and TKA on complications, surgical interventions, quality of life (QoL), pain and costs.

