## **8. METHODS**

### **8.1 Study parameters/endpoints**

#### **8.1.1**

##### **Main study parameter/endpoint**

- Clinical: PROMIS physical function
- Process (healthcare consumption): number of clinical visits and X-rays

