### 8.1.2

#### **Secondary study parameters/endpoints**

- Number and type of complications (e.g. infection, peri-prosthetic fracture, loosening, malalignment or malposition of components, prosthetic wear, dislocation, etc.)
- Number and type of surgical interventions (e.g. DAIR, partial component exchange, revision surgery (full prosthesis replacement), irrigation and debridement (without component retention), etc.)
- Additional healthcare consumption related to THA or TKA FU (e.g. clinical visit, telephone consultations, X-ray, CT scan, MRI scan, laboratory tests, other)
- Health related quality of life (EQ-5D-5L)
- Numeric Pain Rating Scale (NPRS)
- Numeric Satisfaction Rating Scale (NSRS)
- Costs (based on electronic patient records and additional questionnaires, including all visits to healthcare providers outside the hospital)

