**\*A maximum window of  $\pm 30$  days will be applied for data collection of the questionnaires.**

*PROMIS physical function* will be obtained using computer-adaptive testing (CAT). If this is not feasible, the short form (SF) can be completed either digitally or on paper. Version 10a will be used. The SF PROMIS physical function consists of 10 questions and is expressed by raw summed score ranging from 10 to 50, which can be converted to a T-score and SE. The T-score is a standardized score with a mean of 50 and a SD of 10.

*Health related quality of life (EQ-5D-5L)* is a general health-related quality of life questionnaire and consists of five questions regarding mobility, self-care, usual activities, pain/discomfort and anxiety/depression and one visual analog scale (VAS) to document the perceived quality of life. The quality of life is described by 2 scores, the index value, which range from 0 to 1, and the VAS score, which range from 0 to 100. For both scores applies the higher the better.

*Numeric Rating Scale for pain (NPRS)* is a scale ranging from zero to ten on which patients can score their pain. It is a widely used instrument in varying populations due to its ease of administration and clinical relevance to the patient. The lower the score, the better.

*Numeric Rating Scale for satisfaction (NSRS)* will be measured by a single question: “How satisfied are you with the results of the treatment?” The patient will answer this question with a NRS scale ranging from zero to ten. The higher the score, the better.

*Health consumption and costs* will be measured using the EPD. Health consumption includes both the primary outcomes clinical visits and X-rays, as well as additional health care use, including telephone consultations and scans. The LROI register will be used to collect data about revision surgery. A questionnaire will be used to get more insight in the health consumption and costs which cannot be obtained from the EPD. This questionnaire is made in collaboration with a HTA expert and patient representatives.

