### **10.1 Primary study parameter(s)**

PROMIS physical function will be presented as mean with standard deviation, assuming normality. Differences in PROMIS physical function between the RFU and COD groups will be compared using linear mixed models, with repeated measurements clustered within participants and participants clustered within hospitals (random intercepts). The intervention group (RFU vs. COD), baseline PROMIS physical function, and time points (12, 15, 18 and 24) will be included as fixed effects to determine the crude effect of the intervention at each time point, with the primary outcome at 24 months. Given the stepped wedge design, the duration of the intervention period differs between sites. Therefore “period” is also included as a fixed effect. To assess of the effect of COD might increase over a longer period of time, an interaction term (period \* intervention) will be tested for these possible time effects for the primary outcome.

For healthcare consumption, the percentage of patients who have had at least one clinical visit or X-ray 1 year after RFU or COD will be presented for each group. Additionally, the average number of visits and X-rays per patient will be reported.

A logistic generalized linear mixed model (GLMM) will be used to compare the presence or absence of visits/X-rays (yes/no per patient) between RFU and COD. A Poisson regression analysis will be performed to assess the average number of visits and X-rays per patient, adjusting for potential confounders. Interaction terms between the confounders and the intervention group will also be included to explore whether certain patient characteristics influence the differences in healthcare consumption between RFU and COD.

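### The process main outcome is stated inconsistently across the protocol, has no deciding contrast, and leaves open whether the scheduled 1-year visit and X-ray count

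*Protocol*

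**What the plan says.** The process outcome appears in these forms:

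- **Section 2, primary objective:** the effect is sought "on physical function (effectiveness) and clinical visits (implementation". X-rays are not mentioned.
- **Section 8.1.1:** "Process (healthcare consumption): number of clinical visits and X-rays", which is a count of two items.
- **Summary:** "The process outcome is healthcare consumption, including X-rays and clinical visits", which is an open list.
- **Section 8.3, text after Table 2:** "Health consumption includes both the primary outcomes clinical visits and X-rays, as well as additional health care use". Visits and X-rays are here primary outcomes, in the plural, and separate from other care.
- **Section 8.1.2, secondary endpoints:** "Additional healthcare consumption related to THA or TKA FU (e.g. clinical visit, telephone consultations, X-ray". Both items appear again, now as secondary.
- **Section 10.1, descriptive:** "the percentage of patients who have had at least one clinical visit or X-ray 1 year after RFU or COD", and also the mean number of each per patient.
- **Section 10.1, models:** a logistic mixed model to "compare the presence or absence of visits/X-rays (yes/no per patient) between RFU and COD", and then "A Poisson regression analysis will be performed to assess the average number of visits and X-rays per patient", adjusted for confounders.

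Section 10 has all analyses done separately for hip and knee. Section 4.4 gives a margin, confidence level and power for PROMIS only. No hypothesis, alpha, expected rate or success rule is stated for the process outcome.

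**The concern.** This is a hybrid type II trial, so the process outcome carries the de-implementation claim alongside PROMIS. For PROMIS, section 10.1 singles out 24 months among several time points. For the process outcome it makes no such choice. Different readers could cite sections 2, 8.1.1 or 10.1 for different main outcomes, and each would be following the protocol.

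The scales also answer different questions. The yes/no outcome asks how many patients come back at all. The count asks how much care is used, and that drives workload and cost. Fewer patients may return under COD while those who do return come more often, or the reverse.

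The window adds a second gap. Follow-up runs to 2 years, which section 8.3 equates with 1 year after RFU or COD, and section 8.1.3 lists consumption up to one year as a separate parameter. The scheduled 1-year RFU visit and X-ray fall on that boundary. Whether they count decides whether the comparison is informative or nearly settled by the design.

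**Working it through.** **1. The plan's own figure.** Inputs from section 4.4: margin 3, SD 9, one-sided 2.5%, power 90%, no true difference.

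n = 2 × (1.960 + 1.282)² × 9² / 3² = 2 × 10.51 × 9 ≈ 189.2, rounded up to 190 per group.

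This reproduces the protocol. With 24% loss, 190 / 0.76 = 250, inside the stated 20% to 25%. The figure concerns PROMIS only and gives no help on which process contrast was meant. I use 190 per group below as the analysed number.

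**2. Can the yes/no and the count disagree?** The protocol gives no visit rates, so every rate here is an assumption. Each patient is a user with probability p, and a user has 1 + Poisson(m − 1) contacts, so the mean per patient is p × m. The tests are a two-proportion z test and a Wald test on the log rate ratio, with z = ln(total₁/total₂) / √(1/total₁ + 1/total₂). Both are two-sided at 5%, with no clustering. Disagreement means that one is significant and the other is not.

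| Assumed pattern, RFU vs COD | Mean per patient | Yes/no significant | Count significant | Disagree |
|---|---|---|---|---|
| 30% vs 30% users, 1.5 contacts each | 0.45 vs 0.45 | 5% | 10% | 7% |
| 30% vs 20%, 1.3 each | 0.39 vs 0.26 | 62% | 60% | 14% |
| 40% vs 30%, 1.5 each | 0.60 vs 0.45 | 53% | 52% | 17% |
| 30% vs 30%, 2.0 vs 1.4 | 0.60 vs 0.42 | 5% | 65% | 65% |
| 40% vs 28%, 1.5 vs 2.1 | 0.60 vs 0.59 | 70% | 13% | 67% |
| Scheduled visit counted: 95% vs 30%, 1.2 vs 2.0 | 1.14 vs 0.60 | 100% | 100% | 0% |

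The first five rows leave the scheduled visit out, and disagreement runs from 7% to 67%. The last row counts it, and disagreement vanishes.

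One further pattern: 30% vs 20% users with 1.3 vs 2.0 visits each, so means of 0.39 and 0.40. The yes/no test shows a reduction in about 61% of trials and the count test in about 5%. Repeated runs put the yes/no-only result at 56% to 59%. A count test with a robust variance gives 61% for yes/no only, so this conflict does not come from Poisson overdispersion.

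**3. How many tests, and at what cost?** The narrowest reading of section 10.1 is two tests per joint: a combined yes/no and a combined count. If visits and X-rays are counted separately, there are three. Assume each is two-sided at 5% and that a claim could rest on any one of them.

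- Two independent tests: 1 − 0.95² = 9.75%. With correlation 0.5 it is 9.1%, and with 0.8 it is 7.8%.
- Three independent tests: 1 − 0.95³ = 14.3%. With correlation 0.5 it is 12.6%, and with 0.8 it is 9.8%.

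The correlated values are simulated. The yes/no and the count of the same visits correlated at about 0.87 in simulation, so the lower end is the more realistic for that pair.

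**The case against.** The strongest reply has four parts.

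- **Both analyses are committed to.** Section 10.1 says that both will be run and reported, and ranking two models is often left to an SAP, which section 12.1 foresees. A reader might infer that the sponsor will choose the favourable scale after seeing the data. The text does not support that. What stands is narrower: which variable is the main endpoint is a protocol matter, and the protocol names several.
- **The error rate presumes a rule.** A reader might infer that several confirmatory tests are each planned at full alpha. No alpha or success rule is stated for this outcome, so any inflation is conditional. If the scheduled visit counts, the null is false by design and a false-positive rate has no meaning.
- **Conflict is not the expected result.** The large disagreement figures need contacts per user to differ between arms, and no part of the protocol suggests such a pattern. With equal contacts per user and a real difference, disagreement is 14% to 17%. A reader should not take a figure near 60% as a forecast.
- **The overlap is partly handled.** Section 8.3 separates visits and X-rays from additional care such as telephone consultations and scans. The list in section 8.1.2 may therefore be loose wording, but it still contradicts section 8.3.

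None of this reconciles sections 2, 8.1.1 and 10.1, or settles the scheduled visit.

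**Conclusion.** The point holds as an inconsistency in a main endpoint. Its components (visits, or visits and X-rays), its scale (yes/no or count) and its treatment of the scheduled 1-year contact are not fixed, and nothing says which contrast decides.

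The size depends on what the protocol leaves open. With the scheduled visit and X-ray counted, every version shows lower use under COD almost automatically. With them left out, yes/no and count can diverge. Across both cases disagreement ranges from 0% to about 67% of simulated trials, under assumed rates, 190 patients per group and no clustering. The chance of at least one false positive per joint, about 8% to 10% with two tests and 10% to 14% with three, holds only if any single test could support a claim.

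This should be corrected. It does not invalidate the trial.

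**What to change.** - Name one process primary per joint. The number of hospital visits per patient is one option: it agrees with section 2 and with the visit part of section 8.1.1.
- State its window, and state whether the scheduled 1-year RFU visit counts. Do the same for the X-ray where X-rays are reported.
- Analyse it with one model that carries the hospital random effect and the period term already planned for PROMIS. Section 10.1 names neither for the Poisson regression, so that model needs a small change if a count is chosen.
- Use the same definition in the Summary and in sections 2, 8.1.1, 8.3 and 10.1.
- Keep X-rays and the other scale as supportive, with estimates and intervals and no confirmatory claim.
- Take clinical visits and X-rays out of the additional healthcare consumption item in section 8.1.2, in line with section 8.3.

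The cost is wording in these sections and in any SAP, plus the change to the count model. Data collection and sample size are unaffected.

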## 3. STUDY DESIGN

This study has been developed in collaboration with stakeholders, as part of the Zorgevaluatie & Gepast Gebruik (ZE&GG) program. The stakeholders include clinicians, general practitioners, physiotherapists, patient representatives, epidemiologists, a cost-effectiveness expert, health insurers, guideline developers, and implementation experts. During a co-creation phase, multiple meetings were held in which the diverse interests and expertise of these stakeholders were integrated into the study design. Their continued involvement will guide the study's progress and implementation throughout the project.

This is a hybrid effectiveness (de-)implementation trial type II (17), with a stepped-wedge cluster trial design. A total of 10 hospitals will transition from a period with RFU to a period with COD, with a wash-out period (transition) of 2 months. The aim is to gradually de-implement RFU, with all centers eventually using COD as the standard of care. The inclusion period will last 14 months, followed by a 2-year follow-up for each patient. The total duration of data collection will be from July 2025 (first patient inclusion) to August 2028 (last patient, last visit).

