**Table 1. Monthly patient inclusion per center in a stepped wedge design.**

| Period | Center 1                      | Center 2   | Center 3   | Center 4   | Center 5   | Center 6   | Center 7   | Center 8   | Center 9   | Center 10  | Total |            |
|--------|-------------------------------|------------|------------|------------|------------|------------|------------|------------|------------|------------|-------|------------|
|        | Anticipated included patients |            |            |            |            |            |            |            |            |            |       | Cumulative |
| Jul-25 | 4                             | 4          | 4          | 4          | 4          | 4          | 4          | 4          | 4          | 4          | 40    | 40         |
| Aug-25 | 6                             | 6          | 6          | 6          | 6          | 6          | 6          | 6          | 6          | 6          | 60    | 100        |
| Sep-25 | 10                            | 10         | 10         | 10         | 10         | 10         | 10         | 10         | 10         | 10         | 100   | 200        |
| Oct-25 | 10                            | 10         | 10         | 10         | 10         | 10         | 10         | 10         | 10         | 10         | 100   | 300        |
| Nov-25 | Transition                    | Transition | 10         | 10         | 10         | 10         | 10         | 10         | 10         | 10         | 80    | 380        |
| Dec-25 | Transition                    | Transition | Transition | Transition | 10         | 10         | 10         | 10         | 10         | 10         | 60    | 440        |
| Jan-26 | 10                            | 10         | Transition | Transition | Transition | Transition | 10         | 10         | 10         | 10         | 60    | 500        |
| Feb-26 | 10                            | 10         | 10         | 10         | Transition | Transition | Transition | Transition | 10         | 10         | 60    | 560        |
| Mar-26 | 10                            | 10         | 10         | 10         | 10         | 10         | Transition | Transition | Transition | Transition | 60    | 620        |
| Apr-26 | 10                            | 10         | 10         | 10         | 10         | 10         | 10         | 10         | Transition | Transition | 80    | 700        |

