| May-26 | 10                            | 10         | 10         | 10         | 10         | 10         | 10         | 10         | 10         | 10         | 100   | 800        |
| Jun-26 | 10                            | 10         | 10         | 10         | 10         | 10         | 10         | 10         | 10         | 10         | 100   | 900        |
| Jul-26 | 6                             | 6          | 6          | 6          | 6          | 6          | 6          | 6          | 6          | 6          | 60    | 960        |
| Aug-26 | 4                             | 4          | 4          | 4          | 4          | 4          | 4          | 4          | 4          | 4          | 40    | 1000       |
| Total  | 100                           | 100        | 100        | 100        | 100        | 100        | 100        | 100        | 100        | 100        | 1000  |            |

|                          |
|--------------------------|
| Routine follow-up (RFU)  |
| Check-Up On Demand (COD) |

**Note:** The numbers per month represent the inclusion of patients with either THA or TKA, starting with 2 patients per month for each surgery, followed by 3 patients per month, and then 5 patients with THA and 5 patients with TKA per month.

The order in which the ten hospitals transition from RFU to COD will be determined through randomization. Randomization at the center level enhances the study's methodological rigor, reducing potential biases and increasing the generalizability and strength of the evidence. Besides, the study will be nested in the LROI database, which facilitates long term FU to monitor revision surgeries and mortality beyond the current projects timeline, with minimal additional effort.

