### **4.4 Sample size calculation**

We carefully considered the number of patients needed to obtain reliable estimates of the outcomes with the co-creating stakeholders and also asked orthopaedic surgeons for their opinion of convincing evidence. The agreed sample size is 250 patients per group. To provide a rough indication of the statistical power, we used the online power calculator tool available on Sealed Envelope (18). If there is truly no difference between COD and RFU, 190 patients (per intervention group) are required to be 90% sure that the lower limit of a one-sided 97.5% confidence interval will be above the non-inferiority limit of 3 on the PROMIS score with a standard deviation of 9. Anticipating 20-25% loss to follow up, we will include 250 patients per study intervention group (RFU and COD), thus a total of 500 THA and 500 TKA patients.

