### **10.2 Secondary study parameter(s)**

For complications, surgical interventions, and additional healthcare consumption, the percentage of patients who have experienced each will be presented for each group.

Additionally, the total number of complications, interventions, and additional healthcare consumption per patient will be reported. Logistic GLMM will be used to compare the presence or absence of complications, surgical interventions, and additional healthcare consumption (yes/no per patient) between RFU and COD. A Poisson regression analysis will be performed to assess the total number of complications, interventions, and additional healthcare consumption per patient, adjusting for potential confounders.

Quality of life (EQ-5D-5L) and pain (NPRS) will be analysed using mixed models, with repeated measures clustered within participants and participants within hospitals (random intercepts). Intervention group (RFU vs. active COD vs. passive COD), baseline score, and time (15, 18 and 24 months) are included as fixed effects. Satisfaction (NSRS) will be analyzed using independent t test to compare the mean difference between the RFU and COD group.

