### **10.3 Cost-effectiveness**

The trial-based economic evaluations will focus on the primary outcome (PROMIS physical function) and QALYs, following the intention-to-treat principle. Two perspectives will be considered: 1) healthcare and 2) societal. QALYs will be calculated by multiplying utility values (based on EQ-5D-5L and valued using the Dutch tariff) by health state durations (22,23). Resource utilization will be assessed via cost questionnaires (15, 18 and 24 months after surgery) and valued according to the “Dutch manual of costing” (24). Missing data will be handled with multivariate imputation by chained equations (25). Societal costs include healthcare, absenteeism, presenteeism, unpaid productivity, and informal care; healthcare costs cover only the formal Dutch healthcare sector. Linear mixed models will estimate cost and effect differences, accounting for clustering (e.g., hospital level). Incremental cost-effectiveness ratios (ICERs) will be calculated as cost differences divided by effect differences, with uncertainty assessed through non-parametric bootstrapping nested within multiple imputation. Results will be visualized in cost-effectiveness planes and acceptability curves (26,27). Sensitivity analyses, including complete-case analysis, will test result robustness (23). The budget impact analysis (BIA) will use ZonMw’s BIA tool, based on Dutch incidence data. Perspectives include societal, government (Budget Kader Zorg), and insurer. Scenarios include: 1) RFU-only implementation, 2) COD for all patients, and 3) COD for specific subgroups (e.g., low-complication risk), defined by study results. Costs will be valued using Dutch standard costs, tariffs set by the Dutch Healthcare Authority (NZA), or average insurer tariffs. The cost-effectiveness and BIA analyses will adhere to the 'Dutch guideline for economic evaluations in health care' (28).

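### Calendar period is in the PROMIS model only; the EQ-5D-5L/NPRS model, the NSRS t test and the Poisson regressions leave it out, and the last two also lack a hospital term

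*Protocol*

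**What the plan says.** On the crossover, Section 3 states: "A total of 10 hospitals will transition from a period with RFU to a period with COD, with a wash-out period (transition) of 2 months". Only the sequence of crossover is random: "The order in which the ten hospitals transition from RFU to COD will be determined through randomization". A patient's condition therefore follows from the centre and the inclusion date.

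For PROMIS physical function, Section 10.1 specifies a linear mixed model with a hospital random intercept and adds period as a fixed effect. It justifies this by the stepped-wedge design and the unequal length of the intervention period across sites.

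The other analyses are described differently:

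- **Visits and X-rays (main endpoint), counts, Section 10.1:** "A Poisson regression analysis will be performed to assess the average number of visits and X-rays per patient, adjusting for potential confounders". Section 10.2 uses the same kind of model for counts of complications, surgical interventions and other healthcare use.
- **The same outcomes as yes/no, Sections 10.1 and 10.2:** logistic GLMM, terms not listed.
- **EQ-5D-5L and NPRS, Section 10.2:** mixed model with a hospital random intercept; the listed fixed effects are group, baseline score and follow-up time.
- **NSRS, Section 10.2:** "Satisfaction (NSRS) will be analyzed using independent t test to compare the mean difference between the RFU and COD group".
- **Costs and effects, Section 10.3:** "Linear mixed models will estimate cost and effect differences, accounting for clustering (e.g., hospital level").

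Section 10.4 describes the adjustment variables as patient, surgical and postoperative characteristics.

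**The concern.** In a stepped wedge, treatment and calendar time are tied together by construction. A comparison that leaves calendar time out is close to a before-versus-after comparison: a season, a change in local practice or a change in access to care appears as an effect of COD. Randomising the crossover order protects against this only if the analysis uses the months in which both conditions run side by side.

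The protocol accepts that the design calls for a period term for one outcome. The same reasoning applies to the others, including visits and X-rays, which Section 8.1.1 names as a main endpoint, and the complication counts, which bear on whether dropping the 1-year visit is safe. Patients of one hospital also share practice, so an analysis that treats all patients as independent will usually report intervals that are too narrow.

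**Working it through.** **Inputs.** Monthly inclusions come from Table 1 ("Monthly patient inclusion per center in a stepped wedge design"). Its shading is lost in the text, so months before a centre's transition are read as RFU and months after it as COD. Section 10 analyses THA and TKA separately. Calendar drift, ICC, event rate and between-hospital spread are assumptions, because the protocol gives none.

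**1. The plan's own figure.** Section 4.4 states that "190 patients (per intervention group) are required to be 90% sure that the lower limit of a one-sided 97.5% confidence interval" clears a margin of 3 with SD 9. n = 2 × 9² × (1.9600 + 1.2816)² / 3² = 18 × 10.508 = 189.1, rounded up to 190. With 24% loss, 190 / 0.76 = 250. Table 1 sums to 500 RFU and 500 COD, which is 250 per group per joint. The schedule and the sample size agree.

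**2. When each arm is recruited (Jul-25 = month 0).**

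| Month | 0 | 1 | 2 | 3 | 4 | 5 | 6 | 7 | 8 | 9 | 10 | 11 | 12 | 13 |
|---|---|---|---|---|---|---|---|---|---|---|---|---|---|---|
| RFU | 40 | 60 | 100 | 100 | 80 | 60 | 40 | 20 | 0 | 0 | 0 | 0 | 0 | 0 |
| COD | 0 | 0 | 0 | 0 | 0 | 0 | 20 | 40 | 60 | 80 | 100 | 100 | 60 | 40 |

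- Mean RFU month = 1560 / 500 = 3.12. Mean COD month = 4940 / 500 = 9.88. Gap = 6.76 months.
- Both conditions recruit only in months 6 and 7: 60 + 60 = 120 of 1000 patients.

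**3. Bias from a drift, with no COD effect.** The spurious rate ratio is about exp(6.76 × monthly log-drift).

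- Rising 1% or 2% per month: exp(0.0676) = 1.07; exp(0.1352) = 1.14.
- Falling 1% or 2%: 0.93; 0.87.
- A hospital random intercept without period does not remove it. By generalised least squares on this schedule, the bias is 6.9-7.1 times the monthly trend for ICC 0.01-0.10.

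**4. Ignoring hospital, one joint, 250 per group.** Each hospital's net weight in the difference of means is (COD − RFU) / 250. This is ±0.08 for four hospitals, ±0.04 for four and 0 for two. The squares sum to 4 × 0.0064 + 4 × 0.0016 = 0.032. In units of the total variance:

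- naive variance = 2 / 250 = 0.008
- true variance = 0.008 × (1 − ICC) + 0.032 × ICC
- ratio = 1 + 3 × ICC = 1.03, 1.15 and 1.30 at ICC 0.01, 0.05 and 0.10
- two-sided type I error = 2 × (1 − Φ(1.96 / √ratio)) = 5.3%, 6.8% and 8.6%

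**5. Simulated Poisson regression, no true COD effect.** Assumptions: 250 per group, mean of 1 event per patient at month 0, hospital SD on the log scale 0, 0.2 or 0.4, 800 runs each, nominal 5% test. The adjusted model uses hospital indicators and linear time.

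| Drift | Arm only: rejects | Hospital + linear time: rejects |
|---|---|---|
| none | 3%, 7%, 14% | 4-5% |
| −2% per month | 26%, 30%, 33% | 3-5% |

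**6. What adjustment costs.**

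- *Month effects.* Arm varies within month only in months 6 and 7: 2 × 60 × (2/3) × (1/3) = 26.67, out of 1000 × 0.25 = 250. The variance inflation is 250 / 26.67 = 9.4.
- *Linear time.* The correlation of arm with month is 0.8783, so the inflation is 1 / (1 − 0.8783²) = 4.4.
- With a hospital random intercept and ICC up to 0.10, these rise to 10.3 and 5.0.

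**The case against.** The best defence is that a protocol need not list every model term and a statistical analysis plan may supply them. That stands for the logistic GLMMs and the cost models: the text is silent, and the cost models do account for hospital. A reader might infer that every model other than PROMIS rejects period; the documents do not support that. The defence is weaker elsewhere. The EQ-5D-5L/NPRS fixed effects are enumerated, a t test has no room for either term, and the Poisson regressions name only confounders, which Section 10.4 describes without calendar time.

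A reader might also infer that the process, safety and cost results are confounded as a matter of fact. They are exposed to confounding; bias appears only if outcomes drift, and the protocol gives no drift. For visits and X-rays, much depends on whether the scheduled 1-year contact is counted. If it is, the contrast is largely built into the design and a spurious ratio of 1.07-1.14 is unlikely to change the conclusion. If counting starts afterwards, it could. Section 10.1 is ambiguous on this.

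Two further inferences go too far. That the Poisson model fails through overdispersion rests on a variance the documents do not give. That "Interaction terms between the confounders and the intervention group will also be included" distorts the main intervention coefficient is a contestable reading: the stated aim of those terms is exploratory, and Section 10.5 puts interactions in separate models. Both are at most optional clarifications.

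Finally, adjustment is expensive here, and it would be wrong to call it a minor change. That objection stands in full, but the loss comes from the schedule; leaving period out only hides it.

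**Conclusion.** The concern holds in graded form. As written, the EQ-5D-5L/NPRS model omits period, the NSRS t test omits period and hospital, and the Poisson regressions name neither although they serve a main endpoint. These do not fit the design, and they are inconsistent with the PROMIS model in the same chapter. For the logistic and cost models the finding is only that the period term needs to be stated.

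The 6.8-month gap and the 120-of-1000 overlap follow from Table 1 without further assumption. The rate-ratio bias depends on the assumed drift and is absent without one. The variance understatement depends on the assumed ICC and applies only to the Poisson and t-test analyses; it is modest at an ICC of 0.01. The simulated rejection rates also depend on the assumed event rate and hospital spread.

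**What to change.** State in Section 10 that every RFU-COD comparison includes calendar period as a fixed effect and a hospital random intercept, and define how period is coded. Specifically:

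- make the count regressions in 10.1 and 10.2 mixed models with both terms;
- add period to the EQ-5D-5L/NPRS list and to the cost and effect models in 10.3;
- name both terms for the logistic GLMMs;
- replace the NSRS t test with a linear mixed model with both terms;
- where events are rare, allow a linear or low-order time term in place of month effects.

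As an optional clarification, say how overdispersion would be handled and that the main process effect is read from a model without confounder interactions.

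No new data and no change in conduct are needed. The cost is precision: standard errors of the COD effect grow by about √4.4 to √5.0, or 2.1-2.2 times, with linear time, and by √9.4 to √10.3, or 3.1-3.2 times, with month effects. For rare complications little information may remain. The protocol should say so in advance and fix the coding of period before any data are seen, because the choice between linear time and month effects roughly doubles the variance.
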